### Study procedures

#### Recruitment

Potential patients who have been diagnosed with stroke and/or their carer will be identified by clinical staff (e.g. neurologist, nurse) and provided with a study flyer. Patients and/or carers will be asked permission for a researcher to approach them to discuss the program in more detail. If agreeable, they will be approached, informed and formally consented by the research assistant. Study fliers will also be posted online through community organisations and will include contact details for the research team. Participants from the community may contact researchers directly to request further information. Planned recruitment will occur over an 18-month period (see Fig. 1).

**Fig. 1 Fig1:**
[figure not shown]
Flowchart of the Stroke and Carer Optimal Health Program (SCOHP) randomised controlled trial (RCT)

#### Consent

The process of consent will be in accordance with the Declaration of Helsinki. Nurse unit managers were consulted to determine a patient’s eligibility for the study. Senior clinicians and the research team were consulted in instances when it was unclear if an individual met the inclusion criteria. All eligible patients and carers will be fully informed that they are being asked to participate in an RCT. The procedures involved in the study, and the chances of being assigned randomly to one of two groups will be explained verbally and via an information sheet approved by the hospital’s Human Research Ethics Committee. A signed consent form will be obtained from each participant. Participants will be made aware of their right to withdraw from the study at any time without any effects on their clinical management.

#### Randomisation and blinding

Using a computer-generated block randomisation sequence created by a researcher independent of the study, participants will be allocated to treatment or control group. The allocation sequence will be generated using random numbers and participants will be randomised progressively as they consent. Patients and carers will be randomized as dyads. Patients or carer will be randomized alone if they are not participating as a dyad. Due to the nature and length of the intervention, it is not possible to blind either participant or investigator to the treatment allocation.

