### Participants

A total of 84 patients diagnosed with stroke, and 84 carers of these patients, will be recruited into the RCT. For the purposes of this study, stroke is defined as cerebral infarction or parenchymal haemorrhage confirmed by medical records. The following criteria are to be met for inclusion into the RCT: (1) diagnosis of stroke for patient or self-nominated carer of a stroke patient; (2) 18 years or older; (3) ability to converse in English without an interpreter or professional assistance; (4) absence of developmental disability or amnestic syndrome impairing their ability to learn from the intervention; and (5) absence of serious comorbid illness, including severe forms of aphasia, as identified by the nurse unit manager, and cognitive impairment, as identified from medical notes scoring lower than 24 on the Mini-Mental State Examination (MMSE) [27]. As the OHP adopts a holistic approach to managing chronic disease, patients may enter the program at any stage along the continuum of care.

Power was calculated to detect a medium effect size of Cohen’s *d* = 0.50. This was chosen as a clinically meaningful effect size that may be compared with previous RCT research in the area of chronic disease management programs [28]. Calculations assumed two primary outcomes (health-related quality of life and General Self-Efficacy Scale (GSE) scores), four assessment points (baseline, 3-month, 6-month, and 12-month), a study-wide type I error rate (α) of .05, and hence a type II error rate (β) of 0.20 (power of 0.80), a correlation of post-treatment scores with baseline measurements (ρ) of 0.81, and a two-tailed statistical test [29]. To detect an effect size of Cohen’s *d* = 0.50, 53 participants in each of the control and intervention groups will be required. Allowing for up to 20 % attrition, a total of 168 participants, or 42 carers and stroke survivors in control and intervention groups will be recruited.

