#### Intervention: SCOHP

The SCOHP is delivered at a nominated place of convenience by the participant i.e. home, hospital, community health centre. Dyads have the option of either receiving the intervention independently or together. The SCOHP comprises a modular format of eight sequential sessions plus a booster, based on a structured workbook. Participants are encouraged throughout the program to identify areas of stroke- or carer-related health concerns on which they would like to focus. Sessions are approximately 1 hour in duration and held weekly, apart from the ‘booster’ session, which is held 3 months after session 8. Learning is cumulative with each session designed to build on the previous session including tasks to complete between sessions, i.e. journaling and coping strategies (e.g. breathing exercises).

In summary, session 1 introduces SCOHP within the six domains of the ‘Optimal Health Wheel’: social, physical, emotional, intellectual, employment and spiritual as documented in the workbook. This session provides participants with the opportunity to explore and understand stroke self-management behaviour from a holistic perspective. Sessions 2 and 3 initiate development of a health plan exploring the implications and potential complications of stroke in terms of strengths and vulnerabilities, and understanding and monitoring disease impact (e.g. emotional burden and physical weakness). Session 4 focuses on medication management and metabolic monitoring. Session 5 expands the health plan to include key stroke partnerships and supports in the community and online (e.g. www.strokefoundation.com.au). Change enhancement is the focus in session 6, in terms of understanding past events and establishing new proactive avenues for change. The aim of session 7 is goal setting via creative problem solving and planning around the complexities of stroke. To cement a shift in focus of the person’s illness from being ‘dependent on’ services to being ‘supported by’ services, session 8 strategises stroke advanced care planning that incorporates wellbeing maintenance and sustainability. The goal of the ‘booster session’ (session 9) is to review health plans, consolidate progress, and reflect on achievements towards health-related goals.

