#### Outcome measurements

Table 2 details the primary and secondary outcome measures and time points for carers and stroke survivors. Participants complete the measures independently unless a specific request is made for assistance e.g. due to vision or motor skill impairment. Primary outcome measures for both stroke survivors and carers are quality of life and self-efficacy. Health-related quality of life will be assessed using the (AQoL-6D) [25], which consists of six dimensions of health and a global ‘utility’ score and the EuroQol-5D (EQ-5D) [26]. Self-efficacy is to be assessed using the General Self-Efficacy Scale (GSE) [31] a measure of perceived self-efficacy in response to daily challenges and stressful life events. Secondary measures for both stroke survivors and carers are: coping strategies as measured using an abbreviated version of the COPE inventory, the Brief COPE [32]; symptom severity and caseness of depression and anxiety disorders as assessed using the Hospital Anxiety and Depression Scale (HADS) [33]; a 10-item measure of the Big Five personality dimensions (BFI-10) [34]; effect of an individual’s mental health on their ability to function via the Work and Social Adjustment Scale (WSAS) [35]; treatment expectancy and rationale credibility of the clinical study as assessed with the Credibility/Expectancy Questionnaire (CEQ) [36]; perceived satisfactoriness of treatment as assessed using the Treatment Evaluation Inventory-Short Form (TEI-SF) [37]; and health care utilisation and its economic impact assessed by the Health Care Utilisation Questionnaire (HCUQ) [30]. Stroke survivors will also be assessed for cognitive and emotional responses to stroke using the Brief Illness Perceptions Questionnaire (BIPQ) [38]. In addition, carers will be assessed for carer strain using the Modified Caregiver Strain Index (MCSI) [39] and carer satisfaction as assessed by the Carer Assessment of Satisfaction Index (CASI) [40].

Due to the potential for variability of ‘usual care’ in the control group, key aspects of usual care will be assessed with the HCUQ. Furthermore, medical records will be reviewed to determine stroke diagnostic information and clinical indices including the Modified Rankin Scale (MRS), which measures the degree of disability/dependence after a stroke.

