#### Statistical analyses

Intention-to-treat analyses will be employed to prevent overestimation of efficacy. Categorical variables will be analysed using chi-squared tests (or Fisher’s exact test for small samples). A mixed-effects model, repeated measures (MMRM) approach will be used to examine the longitudinal profile of continuous variables at 3, 6 and 12 months post-baseline. For all MMRM analyses, baseline scores will be used as covariates and the models will include prespecified fixed effects of treatment, clinician, and time, and treatment-by-time and treatment-by-clinician interactions.

Secondary analyses using analysis of covariance will be conducted to compare change scores during treatment and follow-up phases for primary, secondary, and process outcomes using the fixed, continuous covariate of baseline score as well as the categorical fixed effects of treatment group, clinician, and treatment-by-clinician interactions.

Although the attrition rate is not expected to vary by treatment condition, we will attempt to identify key predictors of attrition status (i.e. demographic and baseline clinical characteristics) and test for differences between conditions. Assuming the data are missing at random, several procedures offer effective approaches that may attenuate attrition. Maximum likelihood models (i.e. MMRM), with time as a random variable, allow the use of all available data from all assessments, reducing bias and increasing power [43]. In addition, multiple imputation procedures that utilise the expectation-maximization (EM) algorithm with bootstrap estimates of standard errors will be used to address attrition. The application of these procedures can provide unbiased estimates, even in the face of substantial missing data [44].

A full economic evaluation will occur alongside the proposed RCT. Healthcare outcomes and costs will be compared between participants in the control and interventional conditions. Healthcare system (medical record) and self-reported information via the HCUQ [30] will be used to generate analyses. The utility measurements of participant quality of life will be assessed using AQoL-6D [25] developed in Australia and the EQ-5D-3L [26] developed in Europe. The potential long-term (lifetime) impact on cost and effectiveness of intervention beyond the trial period will be extrapolated using the Markov process modelling method.

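### Survivors and carers are randomised as pairs, but the sample size counts them as independent and the listed model terms include neither dyad nor role; if the roles are pooled, standard errors will probably be too small

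*Protocol article*

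**What the plan says.** All references are to the Protocol article.

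- **Randomisation and blinding:** "Patients and carers will be randomized as dyads". Unpaired people are covered as well: "Patients or carer will be randomized alone if they are not participating as a dyad".
- **Intervention: SCOHP:** "Dyads have the option of either receiving the intervention independently or together".
- **Participants:** "A total of 84 patients diagnosed with stroke, and 84 carers of these patients, will be recruited into the RCT". The power paragraph requires 53 people per group and recruits 42 survivors and 42 carers per arm, 168 in total. It mentions neither pairing nor a within-dyad correlation.
- **Outcome measurements:** "Primary outcome measures for both stroke survivors and carers are quality of life and self-efficacy".
- **Statistical analyses:** besides the baseline score, "the models will include prespecified fixed effects of treatment, clinician, and time, and treatment-by-time and treatment-by-clinician interactions". This list is given for every MMRM analysis. The one random term named is time: "Maximum likelihood models (i.e. MMRM), with time as a random variable". The secondary ANCOVA uses baseline score, treatment, clinician and their interaction. Neither model has a term for dyad or for role, and nothing says whether survivors and carers are analysed together or apart.

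**The concern.** Where both members take part, the unit of randomisation is the pair. The two people share one allocation, are linked by a caring relationship, may sit in the same sessions, and answer the same two primary questionnaires. Their outcomes are likely to be positively correlated. A model that treats them as independent then understates the standard error of the treatment effect, so the study-wide 5% error rate set in the power paragraph would not be kept.

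There is a second, smaller consequence. The aims and primary outcomes are declared for survivors and carers alike. A pooled model without a role-by-treatment term yields only one averaged effect: true effects of 0.5 SD in one role and 0 in the other would appear as (0.5 + 0)/2 = 0.25 SD, with no indication of who benefits.

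**Working it through.** **Inputs from the protocol (Participants):** d = 0.50; two-sided α = 0.05; power 0.80; four assessments; ρ = 0.81; 53 per group required; 20% attrition; 168 recruited, that is 84 per arm, or 42 per role per arm. **Assumed, because the document gives no value:** a within-dyad ICC, after baseline adjustment, of 0.1 to 0.4.

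**Step 1. Reproduce the stated 53.** The two-sample normal formula gives 2 × ((1.96 + 0.842)/0.5)² = 62.8 per arm. The repeated-measures factor for the mean of four assessments is (1 + 3 × 0.81)/4 = 0.8575. The product is 53.84, so 54 against the stated 53. This is close enough to be the likely basis, and it treats every participant as independent. A baseline-adjusted ANCOVA formula (factor 1 − 0.81²) gives 22 per arm at α = 0.05. At α = 0.025 it gives 26.15 per arm, or 52.3 over both arms together, whereas the protocol says 53 in each group.

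**Step 2. Does one role alone meet 53?** No. There are 42 per arm before attrition and 42 × 0.8 = 33.6 after it. With both roles there are 84 per arm, and 84 × 0.8 = 67.2 after attrition. The stated requirement is met only by adding the roles.

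**Step 3. Error rate if the roles are pooled and pairing is ignored.** The design effect (DE) is 1 + ICC for complete dyads. With independent 20% dropout, a completer's partner also completes 80% of the time, so DE = 1 + 0.8 × ICC. True type I error = 2[1 − Φ(1.96/√DE)].

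| Assumed ICC | 0.1 | 0.2 | 0.3 | 0.4 |
|---|---|---|---|---|
| All in complete dyads | 6.2% | 7.4% | 8.6% | 9.8% |
| All in dyads, independent 20% dropout | 5.9% | 6.9% | 7.8% | 8.8% |
| Half of participants in dyads (simulated) | 5.6% | 6.0% | 6.9% | not run |

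A simulation with 42 complete dyads per arm and 20,000 runs gave 6.3%, 7.3% and 8.5% at ICC 0.1, 0.2 and 0.3, in line with the first row. A dyad-level test on the same data gave 5.1%, 5.0% and 5.0%.

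**Step 4. Power if the roles are pooled.** Effective number per arm = 67.2/DE.

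- Partners drop out together: 61.1, 56.0, 51.7 and 48.0 at ICC 0.1 to 0.4. It falls below 53 when ICC exceeds 67.2/53 − 1 = 0.27.
- Independent dropout: 62.2, 57.9, 54.2 and 50.9. It falls below 53 when ICC exceeds 0.268/0.8, about 0.33.

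At an effective 51.7 per arm, power under the Step 1 formula is still 0.78.

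The room here comes from recruiting 84 per arm, when 53/0.8 calls for only 67. The protocol does not offer pairing as the reason for that surplus, and a surplus does not correct a standard error.

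**Step 5. If the roles are analysed separately.** There is then one person per randomised unit in each model, so the clustering disappears. With 33.6 per arm, the Step 1 formula gives power of 0.60 at α = 0.05 and 0.49 at α = 0.025. The ANCOVA formula would give 0.94 and 0.90, but it is not the one that yields 53 per group.

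**The case against.** The strongest reply is that pooling is an inference. Table 2 sets carers and survivors in separate blocks. The list of terms covers all MMRM analyses, including outcomes measured in one role only (BIPQ in survivors; MCSI and CASI in carers), where a role term could not be fitted. A generic list without role therefore also fits separate models. In addition, the list is one of fixed effects; a dyad covariance is not a fixed effect, and a condensed article may leave covariance structure to a fuller document. This stands as far as it goes: the article does not show that the analysis will be wrong, and the point has to be conditional on pooling. It does not clear the article, because the sample size is fixed in the text, ignores the pairing, and meets its own requirement only when the roles are added.

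Three stronger readings are tempting, and the document does not support them.

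- A reader might infer that exactly 84 units are randomised. Single enrolment is allowed, so the number lies between 84 and 168, and the first row of the table is the extreme case.
- A reader might infer that partners share a household. The article does not say so; the case for correlation rests on shared allocation, optional joint sessions and the caring relationship.
- A reader might infer that omitting role biases the treatment effect. Allocation by dyad roughly balances the roles across arms, so the pooled estimate is not distorted by a missing role main effect. What is lost is the ability to tell the roles apart.

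**Conclusion.** The point holds in conditional form. The pairing created at randomisation is absent from both the sample size and the listed model terms, and neither possible reading is consistent with the text as it stands.

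If the roles are pooled, a nominal 5% test runs at roughly 6 to 10% over an assumed ICC of 0.1 to 0.4. The upper end requires everyone to be in complete dyads; dropout and unpaired participants bring it down. This rests on a positive within-dyad correlation after baseline adjustment, which is plausible but not documented; at zero correlation there is no inflation. The harm is mainly to the error rate: the effective number stays above 53 up to an ICC of about 0.27 to 0.33.

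If the roles are analysed separately, the error rate is not affected by pairing, but 42 per arm (about 34 after attrition) falls short of the stated 53.

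It would go too far to conclude that role-specific effects must be the primary estimates. That is a choice of estimand, and it would turn two primary comparisons into four under a study-wide α of 0.05.

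**What to change.** 1. State whether survivors and carers are pooled, and that the analysis follows the randomised unit.
2. In any pooled model, add a dyad-level random effect or covariance, with unpaired participants as clusters of one, plus role and role-by-treatment terms. Outcomes measured in one role only need none of these.
3. Report the survivor and carer effects as supporting estimates. If they are made primary, state how the study-wide α is shared among the tests.
4. Restate the sample-size basis with the dyad design effect and an explicit ICC. From the 53.84 of Step 1, complete dyads need 60, 65, 70 or 76 completers per arm at ICC 0.1, 0.2, 0.3 or 0.4, against 67.2 expected. If the roles are to be separate, give the calculation that supports 42 per arm.

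**Cost:** these are changes to wording and model specification; no change in recruitment or data collection is called for under pooling, provided the data set identifies who belongs to which dyad. Intervals for a pooled effect widen by √DE, from about 5% at ICC 0.1 to about 18% at ICC 0.4 with everyone in complete dyads, and a few more parameters are estimated. Making the role-specific effects primary would cost more, because it needs an α allocation and its own power check.

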#### Intervention: SCOHP

The SCOHP is delivered at a nominated place of convenience by the participant i.e. home, hospital, community health centre. Dyads have the option of either receiving the intervention independently or together. The SCOHP comprises a modular format of eight sequential sessions plus a booster, based on a structured workbook. Participants are encouraged throughout the program to identify areas of stroke- or carer-related health concerns on which they would like to focus. Sessions are approximately 1 hour in duration and held weekly, apart from the ‘booster’ session, which is held 3 months after session 8. Learning is cumulative with each session designed to build on the previous session including tasks to complete between sessions, i.e. journaling and coping strategies (e.g. breathing exercises).

In summary, session 1 introduces SCOHP within the six domains of the ‘Optimal Health Wheel’: social, physical, emotional, intellectual, employment and spiritual as documented in the workbook. This session provides participants with the opportunity to explore and understand stroke self-management behaviour from a holistic perspective. Sessions 2 and 3 initiate development of a health plan exploring the implications and potential complications of stroke in terms of strengths and vulnerabilities, and understanding and monitoring disease impact (e.g. emotional burden and physical weakness). Session 4 focuses on medication management and metabolic monitoring. Session 5 expands the health plan to include key stroke partnerships and supports in the community and online (e.g. www.strokefoundation.com.au). Change enhancement is the focus in session 6, in terms of understanding past events and establishing new proactive avenues for change. The aim of session 7 is goal setting via creative problem solving and planning around the complexities of stroke. To cement a shift in focus of the person’s illness from being ‘dependent on’ services to being ‘supported by’ services, session 8 strategises stroke advanced care planning that incorporates wellbeing maintenance and sustainability. The goal of the ‘booster session’ (session 9) is to review health plans, consolidate progress, and reflect on achievements towards health-related goals.

A health professional (e.g. nurse, psychologist) trained in the approach (2-day workshop plus regular supervision and fidelity checks) will facilitate each session. The facilitator will draw on carer and stroke-specific information in concordance with individual circumstances. Examples include the relationship between depression and caregiving or physical impairments of stroke, availability of stroke and carer supports in the community, and coping strategies for addressing anxiety and stress related to new roles and circumstances. The emphasis is on collaboration between facilitator and participant to arrive at goals for the program that stem from the participant’s main concerns and needs. The facilitator will encourage participants to identify their early warning signs of stress and illness and integrate healthy coping strategies to prevent the build-up of stress. Facilitators may also discuss and arrange referrals for other services in conjunction with the multidisciplinary team depending on participant needs. Additionally, facilitators will work with the multidisciplinary team to coordinate visits. Participants in rural and regional areas will have the option of participating in sessions via phone or Skype.

